#### Missing data and interpolation strategies

2.7.2 

We will assume missing at random and use multivariate imputation by chained equations (MICE) with fully conditional specification in SAS 9.4, generating 50 imputed datasets and combining estimates via Rubin’s rules. The imputation model will include treatment arm and cluster identifier (ICU) to preserve clustering, plus pre-specified covariates.

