### Sample size calculation

2.3 

Sample size calculation was performed using PASS software. The primary clinical outcome was the difference in the incidence of FI between the two groups. Based on previous studies, the incidence of FI among critically ill patients in the control group was assumed to be 0.5. According to the clinical decision curve analysis from the predictive model for FI (NOFI) (10), the net benefit at a threshold probability of approximately 50% was 0.257, indicating that around 25.7 patients out of every 100 would benefit from the intervention. Therefore, it was assumed that the mNEED protocol (intervention group) would reduce the incidence of FI by 25%, resulting in an expected FI rate of 0.375 in the intervention group [0.5 × (1–0.25) = 0.375]. We set the intraclass correlation coefficient (ICC) to 0.10 by analogy to the NEED trial (4), a total of 45 clusters per group were planned, with an ICC of 0.1. Using a two-sided alpha of 0.05 and a statistical power of 90% (1–β = 0.9), the required number of participants per cluster was calculated to be 25. Thus, the total sample size was 45 clusters × 25 participants × 2 groups = 2,250 participants. We pre-specified ICC sensitivity analyses, which indicated that the planned configuration is robust to plausible ICC and cluster-size variability; detailed results are provided in Supplementary Tables 3, 4.

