#### Handling of incomplete FI assessments

2.6.1.2 

(1). If a patient experiences an ICU disposition (death or discharge/transfer) within 7 days of ICU admission, the FI window spans ICU admission to the time of disposition. (2). If no prespecified gastrointestinal (GI) symptom is documented and the patient has an ICU disposition within 72 h of EN initiation such that FI cannot be fully ascertained, the primary analysis will classify the patient as no FI.

Adjusted FI (aFI) sensitivity definition. For the scenario described in rule (2) above, we prespecify an adjusted FI endpoint (aFI) for sensitivity analyses:

If any EN reduction is recorded, classify as FI

If no EN reduction is recorded, classify as no FI.

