#### Duration of treatment and follow-up

2.6.4 

The study intervention will continue for 28 days following ICU admission, unless the patient is discharged from the ICU, discharged from the hospital, or dies earlier. All randomized patients will be followed for 90 days after ICU admission, unless death occurs first. If a patient remains hospitalized on day 90, follow-up will be conducted and outcomes will be recorded based on the patient’s status on day 90.

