#### Data analysis

2.7.1 

All statistical analyses will be conducted in accordance with a pre-specified statistical analysis plan. The primary analysis will follow the intention-to-treat (ITT) principle, with adjustment for clustering. The primary outcome (FI, binary) will be analyzed using a generalized linear mixed model (GLMM, logit link) with a random intercept for ICU/cluster and fixed effects for treatment and the pre-specified covariates (APACHE II score, AGI grade, primary diagnosis). To guard against model mis-specification and unequal cluster sizes, cluster-robust (sandwich) standard errors will be used for inference with between-cluster degrees of freedom; if convergence or small-sample issues arise, a wild cluster bootstrap-t procedure will be applied as a pre-specified fallback. Operationally, the full analysis set (FAS) will be used, defined as all randomized patients who have at least one valid post-randomization assessment of the primary outcome. The PPS, defined as patients who received protocolized EN for at least 48 h, will be used for sensitivity analyses.

Binary secondary outcomes (e.g., achievement of nutritional targets by day 7) will be analyzed analogously with GLMM (logit); continuous outcomes will use linear mixed models with a cluster random intercept and Kenward–Roger degrees-of-freedom adjustment. In addition, the EFI will be applied as a prespecified sensitivity analysis of the primary outcome to assess the robustness of the findings.

Continuous variables will be summarized as mean ± standard deviation if normally distributed, or as median and interquartile range (IQR, P25–P75) if not normally distributed. Between-group differences in continuous variables will be tested using the independent samples *t*-test for normally distributed data or the Mann–Whitney *U*-test for non-normally distributed data. Categorical variables will be compared using the Chi-square test.

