Sensitivity analyses will include: (i) an unadjusted GLMM (treatment + random intercept only); (ii) a covariate-enriched GLMM that adds baseline mechanical ventilation and sepsis (yes/no; protocol-defined) on top of the pre-specified covariates (APACHE II score, AGI grade, primary diagnosis); and (iii) aFI. All covariates are pre-specified and retained regardless of statistical significance. We will report adjusted odds ratios (95% CIs) for binary endpoints (with marginal risk differences via standardization as supportive estimates). The primary endpoint will be tested at two-sided α = 0.05 without multiplicity adjustment. For prespecified clinical secondary endpoints, we will control the false discovery rate at *q* = 0.05 using the Benjamini–Hochberg procedure (two-sided *p*-values from the specified models). Process outcomes (fidelity, exposure, contamination) are exploratory and will be summarized descriptively with 95% CIs; no hypothesis testing or multiplicity adjustment will be applied to these measures. All analyses will be performed using SAS software version 9.4^®^ (SAS Institute Inc., Cary, NC, United States).

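### The general missing-at-random imputation rule has no exemption for death, so as written it would create quality-of-life and muscle values for patients who died before the visit

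*Protocol article*

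**What the plan says.** The protocol article, section 2.7.2 (Missing data and interpolation strategies), reads: "We will assume missing at random and use multivariate imputation by chained equations (MICE". It specifies 50 imputed datasets combined by Rubin's rules. On the model it says: "The imputation model will include treatment arm and cluster identifier (ICU) to preserve clustering, plus pre-specified covariates". It does not list the variables to be imputed, exclude any patients, or mention survival.

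Section 2.6.2 lists 12 secondary outcomes. Six are measurements that need a living patient at a fixed time: SF-36 and EQ-5D-5L at days 28 and 90, and diaphragm thickness, quadriceps thickness, rectus femoris area and upper limb muscle thickness at day 7. Mortality at days 28 and 90 is listed separately.

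Section 2.6.4 on follow-up says: "All randomized patients will be followed for 90 days after ICU admission, unless death occurs first".

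Section 2.7.1 says of the analysis model: "continuous outcomes will use linear mixed models with a cluster random intercept". It describes no survivor-only, composite or ranked analysis.

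Death is handled in one place, section 2.6.1.2, and for FI only: "If a patient experiences an ICU disposition (death or discharge/transfer) within 7 days of ICU admission, the FI window spans" admission to the time of disposition.

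**The concern.** Missing at random is an assumption about a value that exists but was not observed. A day-90 EQ-5D-5L score or a day-7 scan in a patient who has already died is not such a value. Patients enter this trial with at least one organ failure, and mortality is an endpoint, so deaths before these visits are to be expected.

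Applied without restriction, the rule would give the deceased values predicted from survivors with the same arm, ICU and covariates. The arm contrast would then answer a question about a trial in which nobody dies, and a reader would not know that part of the data was constructed this way. The article posits FI as a mediator between nutrition and prognosis (sections 3 and 3.1), so survival lies on the trial's own hypothesised pathway.

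There is a knock-on effect on multiplicity. Section 2.7.1 says: "For prespecified clinical secondary endpoints, we will control the false discovery rate" by the Benjamini-Hochberg procedure. If the six outcomes belong to that family, their p-values help set the thresholds for the others.

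**Working it through.** **1. The plan's own figure.** No figure in the article bears directly on this point, but the total of 2,250 is the base for the counts below, so I checked it.

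- Inputs (section 2.3): "the incidence of FI among critically ill patients in the control group was assumed to be 0.5"; "resulting in an expected FI rate of 0.375 in the intervention group"; 45 clusters per arm, ICC 0.10, two-sided alpha 0.05, power 90%.
- Pooled two-proportion formula without continuity correction, mean proportion 0.4375: n = [1.960 × √(2 × 0.4375 × 0.5625) + 1.282 × √(0.25 + 0.234375)]² / 0.125² ≈ 329 per arm under individual randomisation.
- Cluster size: m = 329 × (1 − 0.10) / (45 − 329 × 0.10) = 296.1 / 12.1 = 24.47, rounded up to 25.
- Total: 45 × 25 × 2 = 2,250.
- Check: the effective size is 1,125 / (1 + 24 × 0.10) = 330.9 per arm, giving power of 90.2%.

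The sample size reproduces and does not depend on the point made here.

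**2. Which rule reaches a deceased patient.**

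| Outcome | Rule that applies after death |
|---|---|
| FI (primary) | 2.6.1.2: window ends at death, with a classification rule for early disposition |
| 28- and 90-day mortality | Death is the outcome |
| SF-36, EQ-5D-5L, days 28 and 90 | None except the general rule in 2.7.2 |
| Four ultrasound measures, day 7 | None except the general rule in 2.7.2 |

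**3. How many patients.** The article gives no mortality rate. Assuming 15% to 35% dead by day 90: 2,250 × 0.15 = 337.5 and 2,250 × 0.35 = 787.5, so 338 to 788 patients. This counts imputed records. It does not measure bias. No such count is offered for day 7, where ICU discharge will also leave scans missing.

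**4. What the contrast can and cannot show.** Assume a mean EQ-5D-5L index of 0.60 among survivors in both arms, with 20% mortality on mNEED and 25% on control (all assumptions).

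- Deceased imputed from survivors: 0.60 − 0.60 = 0.00.
- Survivors only: 0.60 − 0.60 = 0.00.
- Death scored as 0: 0.60 × 0.80 − 0.60 × 0.75 = 0.48 − 0.45 = +0.03.

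With a survivor mean of 0.70, the last line becomes 0.56 − 0.525 = +0.035. If the mortality rates are swapped between arms, the sign reverses.

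**5. With a severity covariate.** A simulation of 400,000 patients per scenario (individual patients, no clustering) used one severity variable that drives both death and utility. Mean utility was 0.70 at average severity, with no arm effect on utility. Deaths were filled by regression on arm and severity.

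| Mortality, control vs mNEED | Imputed difference | Death scored as 0 |
|---|---|---|
| 24.9% vs 24.8% | 0.001 | 0.001 |
| 24.9% vs 19.5% | 0.000 | +0.037 |
| 25.0% vs 31.1% | 0.001 | −0.040 |

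The imputed contrast stays at about zero whichever arm has more deaths.

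**The case against.** The strongest reply is that section 2.7.2 never says that values of deceased patients will be imputed. It names no variables. Section 2.6.4 ends follow-up at death, so one could hold that nothing is due afterwards and nothing is missing. Section 2.7.1 refers to a separate analysis plan that is not shown and may restrict the rule. This is a fair limit: imputation after death follows from unrestricted wording and is not declared. But the point concerns a rule that the article states, not its silence. The article does treat death at this level of detail for FI, and the general rule is the only one that reaches the other endpoints.

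Three stronger readings are tempting, and the document does not support them:

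- A reader might infer that a mortality difference would be hidden from the trial's results. It would not, because 28- and 90-day mortality are endpoints in their own right.
- A reader might take the 0.03 above as the error caused by imputation. It is not. The survivor-only contrast is also 0.00 in that example, so the 0.03 comes entirely from scoring death as 0. Stopping imputation makes the estimate honest about whom it describes but need not move it.
- A reader might infer that a mortality gap of five points is expected. Section 3 says that the authors do not think mortality will be lower with mNEED, and the article gives no rate for either arm.

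Scoring death as 0 and ranking death worst are choices of estimand on which statisticians may differ. They belong in supportive analyses.

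**Conclusion.** The point holds in a limited form. Followed as written, the rule in 2.7.2 would produce values that cannot exist for up to six of the 12 secondary outcomes, and the contrasts would refer to a population without deaths. The primary FI analysis and the mortality endpoints are untouched.

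The size of the effect is unknown. The count of 338 to 788 patients rests on an assumed 15% to 35% mortality by day 90, and the differences of 0.03 to 0.04 rest on assumed utilities and mortality gaps. The effect on the Benjamini-Hochberg thresholds is possible but cannot be quantified, and the article does not list which outcomes form that family. What does not depend on these assumptions is that missing at random cannot sensibly be applied to a measurement after death.

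**What to change.** Add to 2.7.2: *Values after death are not missing and are not imputed; imputation is limited to patients known to be alive at that visit.* Multiple imputation can still be used for living patients with a missed questionnaire or scan, including those discharged from the ICU before day 7.

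Report SF-36, EQ-5D-5L and ultrasound results as conditional on survival to the visit, next to mortality by arm. Because a survivor-only contrast does not itself capture a mortality difference, add one supportive analysis that counts death, for example the EQ-5D-5L index set to 0 from death or a rank-based analysis with death as the worst outcome. State the choice before any unblinded analysis.

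The cost is wording in the analysis plan. Vital status is already collected, and no new patients or visits are needed. The downside is that the main results for these endpoints must be labelled as conditional on survival, so they are not a comparison of everyone randomised.

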#### Confidentiality and data security

2.7.3 

All data collected from participating centers will be stored in a secure web-based database. Except for the data administrator (the designated research lead at the coordinating center), no other individual will have the authority to modify, alter, or export patient data or information. Strict measures will be taken to ensure the confidentiality and security of all patient information. An independent Data and Safety Monitoring Board (DSMB)—separate from the sponsor, investigators, and coordinating center—will oversee participant safety and trial conduct under a written charter. An independent statistician will prepare unblinded safety summaries for the DSMB at prespecified intervals; the investigative team will remain blinded. The DSMB may issue recommendations (continue, modify, pause, or terminate) based on predefined safety considerations. Strict measures are in place to ensure confidentiality and data security throughout the study.

### Adverse events

2.8 

Adverse events are defined according to the CTCAE by the U.S. National Cancer Institute as any unfavorable medical occurrence in a patient receiving the study intervention, which does not necessarily have a causal relationship with the treatment.

During EN administration, adverse events may include FI, regurgitation, aspiration, or infection. Patients will be closely monitored for FI and laboratory abnormalities. Symptomatic treatment will be provided as needed, and measures such as head-of-bed elevation will be taken to reduce the risk of aspiration.

## Discussion

3 

Developing objective, guideline-based feeding protocols may improve outcomes in critically ill patients. Two of the largest cluster-randomized controlled trials to date have investigated this approach—one conducted by Doig et al. across 27 ICUs in Australia and New Zealand (3), and the other by Ke et al. across 97 ICUs in China (4). Unfortunately, neither feeding protocol resulted in improved clinical outcomes for critically ill patients. This raises critical questions: Is the impact of nutritional interventions inherently limited, or did the implemented protocols fail to provide real benefit to patients? The reasons behind these negative results remain unclear.

Upon reviewing the data from both trials, we observed that the intervention protocols did not effectively reduce the incidence of FI compared to standard care. The association between FI and poor clinical outcomes in critically ill patients has been well documented in multiple studies (15, 16). This led us to a bold hypothesis: feeding strategies may influence clinical outcomes by reducing FI, suggesting that FI could be a potential mediator between nutritional intervention and patient prognosis.

Unlike the two previous cluster-randomized controlled trials, our study did not adopt mortality as the primary endpoint. Nutritional interventions represent only one component of the overall management of critically ill patients, and directly reducing mortality through nutritional strategies alone appears challenging. The prior two trials did not demonstrate a mortality benefit, nor did they show a reduction in the incidence of FI. Therefore, in the present study we selected FI as the primary endpoint, as it is one of the most clinically relevant indicators of nutritional implementation and has been shown to be associated with patient outcomes (15). Although we do not think the mortality of the mNEED group will be lower, we expect it to at least reduce the occurrence of FI, which might also be beneficial.

A recently proposed concept further supports this hypothesis: in early nutrition, “less is more (17, 18).” Full-dose early nutrition may not benefit, and could even harm, critically ill patients by contributing to overfeeding (18). Therefore, a more promising approach may be to minimize FI while maintaining a gradual feeding progression.

Previously, we developed a predictive model for FI in critically ill patients based on variables such as primary diagnosis, APACHE II score, and AGI grade. This model demonstrated good predictive performance and was externally validated. Based on this, we integrated the tool into a revised feeding protocol to explore whether individualized nutrition strategies could improve outcomes. We adopted a cluster-randomized design, as applying two feeding protocols within the same ICU would be impractical and potentially unreliable.

The primary outcome is the incidence of FI within 7 days of ICU admission. We hypothesize that the mNEED protocol will reduce the incidence of FI. Whether it will also improve other clinical outcomes remains to be determined.

### Strengths and limitations

3.1 

This study has several notable strengths. First, the intervention strategy in the experimental group incorporated an FI prediction model, allowing for a relatively individualized feeding approach tailored to each patient’s predicted risk of FI. This individualized element is an important advancement compared with the two previous cluster-randomized controlled trials, which lacked such prediction-based strategies. Second, we selected FI as the primary outcome, hypothesizing a clear mechanistic pathway: nutritional interventions may influence mortality primarily through their effect on FI. Directly targeting mortality as the primary endpoint is challenging, as mortality is influenced by numerous non-nutritional factors and may be too distal an outcome to capture the effect of feeding strategies. Third, rigorous data quality control was implemented: each participating center appointed a data supervisor responsible for auditing bedside feeding records, verifying protocol adherence, and submitting all ultrasound images and feeding records for centralized review. This process substantially minimized bias and ensured fidelity of the intervention. Fourth, by engaging nearly 100 centers across China, this trial helped to standardize nutritional practice nationwide. Given that intensivists are not always fully familiar with every aspect of nutrition guidelines, the trial facilitated broader implementation and dissemination of guideline-based nutritional care.

This study also has important limitations. First, although FI was chosen as the primary outcome, its definition remains debated. Multiple diagnostic criteria exist; in this trial we adopted the widely accepted and relatively objective 2012 ESICM definition for FI, and applied the EFI definition as a prespecified sensitivity analysis. Despite this limitation, we consider FI the most suitable mediator between nutritional interventions and mortality. Second, center effects across nearly 100 ICUs are difficult to fully control. Although we stratified hospitals by level (secondary vs. tertiary) and performed randomization with a fixed seed, heterogeneity may still exist within the same level of hospitals—an inherent limitation of cluster-randomized designs, but also one that reflects the real-world variation in nutritional practice across China (19). Third, the feeding protocol in the control group was not entirely objective. Although based on the 2023 ESPEN guideline, interpretation of some aspects (e.g., initial feeding rate) remained subjective, which may have introduced variability in control group practices. Fourth, despite standardized ultrasound training delivered by CCUSG-certified instructors, operator-dependent variability could not be completely eliminated. Therefore, the change in muscle mass between day 1 and day 7 may be a more robust measure than the absolute value at day 7.

## Ethics and dissemination

4 

### Research ethics approval and consent to participate

4.1 

This study has been approved by the Ethics Committee of the First Hospital of Jilin University (original version: 24k004-001; revised version: 24k004-002). Ethical approval from each participating center will be required prior to patient enrollment. The study will be conducted in accordance with the principles of the Declaration of Helsinki (current version, Fortaleza, Brazil, 2013) and relevant regulations governing medical research involving human subjects.

The trial has been registered with the Chinese Clinical Trial Registry (ChiCTR2400081581): https://www.chictr.org.cn/showproj.html?proj=219477 and with ClinicalTrials.gov (NCT06827275): https://clinicaltrials.gov/study/NCT06827275.

### Confidentiality issues

4.2 

Processes and safeguards will be in place to protect all information stored in the web-based system. Data access will be secure and restricted to authorized users. Network protections will prevent unauthorized access or transfer of data.

Data security is ensured through multiple measures: servers are protected by firewalls, physical access is restricted, and the server is used exclusively for database management. Each participating site will only have access to data from its own patients, not those from other sites in the mNEED trial. All patient data will be de-identified to protect privacy, and no personal identifiers will appear in any publication. Confidentiality will be maintained in accordance with applicable regulations.

